#### Exclusion criteria

Indicate they do not intend to receive further antenatal, postnatal, or PMTCT care at the site;Are not physically and/or emotionally able to complete the informed consent process to initiate/participate in study (mentally ill, drug abuse, etc.).

### Allocation to study arms

The 12 study sites were formed into six pairs, matched on observed characteristics including geographic location and number of HIV-infected pregnant women presenting for antenatal care (during 2016). Map 1 identifies the basic location for each study site, numbered from 1 to 12, which represents the order sites began enrolment (1 was first, 12 was last). The study site names by study arm are: (SOC Arm/EMMA Arm): 6 = Kapsabet District Hospital/1 = Kericho County Referral Hospital; 11 = Kapkatet District Hospital/4 = Transmara District Hospital; 8 = Kombewa County Hospital/5 = Nandi Hills District Hospital; 12 = Ratta Health Centre/3 = Bomet Health Centre; 2 = Longisa District Hospital/9 = Munyuanda Health Centre; 7 = Meteitei-Sub-district Hospital/10 = Bodi Health Centre. The largest sites were matched together and the study team tried to maintain regional balance between the six counties in which the study is being conducted.

**Map 1 Fig1:**
[figure not shown]
Location of study sites (numbers 1 - 12)

Clinics in the intervention arm provide EMMA services to all patients at the study site, so providers are not blind to their treatment assignment. The study, however, enrolls a subset as study participants for prospective records review. Thus, patients are not blinded but all patients at the intervention sites are provided with EMMA services. After enrollment in the study, individuals receive the same services as provided to all patients at their clinic.

### Participant timeline

The participant timeline is detailed in Fig. 1 (Spirit Figure), with additional detail provided in Fig. 2 discussed below in relation to study outcomes.

**Fig. 1 Fig2:**
[figure not shown]
SPIRIT figure (Study timeline)

**Fig. 2 Fig3:**
[figure not shown]
Timeline showing primary (P) and secondary (S) outcomes to be evaluated

#### Recruitment and enrollment

All women with HIV will be informed about the study by the site’s PMTCT clinical staff (nurses and/or Clinical Officers, depending on site) during their first visit for antenatal care. These clinical staff will use study-developed briefing slides to guide this discussion (see Additional file 3 – Briefing Slides). Those interested in participating, where “participation” means the patient allows the study to review their medical record information collected routinely by the site for patient care, will be referred to the study staff at the site. Study staff will then explain the nature of the study, confirm study eligibility, review the informed consent documents, and obtain written informed consent. The study staff member completing consenting procedures will not be the Mentor Mother at the intervention sites. Patients who do not consent to be in the study will be managed as usual at the study site. Those who consent to be in the study will be referred to one of the clinic’s Mentor Mothers once the consenting process is complete. The study will continue enrolling patients until the target sample size for each site is reached.

Mentor Mothers are already part of the PEPFAR supported staff at the study sites. Their recruitment criteria and general assignments for clinics are clearly stipulated in the KMMP NASCOP implementation guidelines [4]. To implement the EMMA strategy, all Mentor Mothers at the intervention study sites will receive EMMA-specific training as well as refresher training on adherence counseling and psychosocial support (based on the original Mentor Mother curriculum). In addition to EMMA-specific training, since this is a research study, all staff participating in the study will undergo ethics training and study specific research training (included CITI certification).

#### Follow-up

After enrollment in the study, other than interactions with the Mentor Mother as part of EMMA activities in the intervention arm, study staff will have no further contact with study participants. Follow-up for data extraction from medical records will continue through 18 months post-partum for each mother enrolled (and 18 months of age for her child).

### Outcomes measures

#### Primary outcomes

Study outcomes are organized along the PMTCT cascade of care (see Fig. 2), from the first ANC visit through 72 weeks post-partum to evaluate adherence to clinic visits (to receive continuous supplies of ART and for infant HIV testing) and retention in care. Successful implementation of the PMTCT services implies that: (1) pregnant women with HIV initiate life-long ART with minimal delay after their first ANC visit (and women already on ART should continue on ART); (2) they continue on treatment through delivery; (3) they continue on treatment after delivery and the cessation of breastfeeding (and continuing for life for their health); and (4) their child completes HIV testing at 6, 24, 48, and 72 weeks so that the infant is known to be uninfected after the cessation of breast feeding or that the infant is diagnosed and initiated on ART early should he/she become HIV-positive.

The three primary outcomes are:P1: the proportion of HIV-positive pregnant women who receive an uninterrupted supply of ART from treatment initiation to delivery;P2: the proportion of HIV-positive pregnant women who receive an uninterrupted supply of ART from delivery to 24 weeks post-partum;P3: the proportion of babies with known HIV results by 72 (± 4) weeks

To operationalize “uninterrupted supply” for primary outcomes 1 and 2, we will follow Haas et al. [15] and calculate the percentage of days covered by drugs dispensed, with ≥ 90% of days covered deemed as uninterrupted.

#### Secondary outcomes

S1: the proportion of women initiating ART within 30 days of their first ANC visit;S2: the proportion of pregnant women with HIV receiving an uninterrupted supply of ART at 24–48 weeks post-partum;S3: the proportion of pregnant women with HIV receiving an uninterrupted supply of ART at 48–72 weeks post-partum;S4: the proportion of infants completing HIV testing at 6 weeks (± 4 weeks), along with the proportion testing positive for HIV;S5: the proportion of infants who complete HIV testing at 24 weeks (± 4 weeks), along with the proportion testing positive for HIV;S6: the proportion completing HIV testing at 48 weeks (± 4 weeks), along with the proportion testing positive for HIV.

### Sample size

Each primary outcome is a proportion and the sample size (360 total, 180 per arm) was developed to be adequate to detect at least a 25 percentage-point improvement in each primary outcome between the two study groups (Arms SOC and SOC + EMMA). To begin, ignoring possible cluster effects, Table 1 first shows the sample size needed to detect a 0.25 proportional improvement between the two study groups, when the base proportion is in the range of 0.30–0.40 (with 5% significance, 80% power, assuming a two-sided test, using sampsi command in Stata 11). Baseline proportions > 0.4 have smaller estimated sample sizes than for 0.4, so they are not reported. Table 1 also shows how the sample size increases when possible clustering effects are included into the sample size calculation (using sampclus in Stata 11). With 12 possible clusters, and an intra-cluster correlation coefficient of 0.04 and 0.05, the sample size increases by 76–130% with six sites allocated to each study arm (and 20–27 patients per cluster).

**Table 1 Tab1:** Sample sizes to detect 25 percentage point difference in study arms (5% significance, 80% power)

SOC	SOC + EMMA	Random sample size SOC/SOC + EMA	Clusters (n)	Intra-cluster correlation (rho)	Total sample size	Per cluster	Implied design effect
0.30	0.55	68/68	12	0.04	120/120	20	1.76
0.40	0.65	70/70	12	0.04	126/126	21	1.80
0.40	0.65	70/70	12	0.05	161/161	27	2.30

Information does not exist at the sites to estimate the needed baseline proportion (e.g. for Arm SOC). In addition, data on patient progression through the PMTCT cascade are notoriously lacking. For example, PEPFAR indicators show the number of infants (< 2 months of age or aged 2–12 months) receiving an HIV test in a calendar month, but the denominator, which would be the number of mothers with HIV who came to the site for a first ANC visit in the past and enough time has elapsed so that they are at least six weeks post-partum, is not reported. Based on the information in Table 1, we propose a sample size of approximately 30 patients per cluster. This number, which is about 10% larger than largest sample size number in Table 1, accounts for patient attrition from the study that is not addressed as study. For example, some patients enrolled in the study may transfer to another site at some point during the study. Adverse pregnancy outcomes unrelated to the study are also possible (e.g. miscarriage), for which infant outcomes would not exist and the women would be transferred from the site’s MCH clinic to the general HIV clinic for further HIV-related care.

### Data collection methods

Follow-up for data extraction will be passive, by medical record review only, and continue through 72 weeks postpartum. This period of time is needed to evaluate long-term retention in care through cessation of breastfeeding, which includes the 72-week (18-month) postnatal period when the patient is managed at the MCH clinic for ART services.

All information required for the evaluation will be extracted from information on patient care routinely collected by the sites in both study arms as well as the additional information routinely collected by the Mentor Mother providing EMMA as part of her interactions with patients.

Before the study begins, study staff will review each site’s patient record system and related data collection procedures and address any systematic problems that will hinder study data collection (e.g. failure to enter visit dates, drugs prescribed, recording negative HIV test results rather than leaving information blank, which have been common problems we have encountered during prior studies at these and other sites).

The study will use three clinical records forms (CRF) for extracting information from the patient’s medical file through 72 weeks post-partum (up to 76 weeks to confirm final HIV test completion for the infant). The three CRFs are included in Additional file 4 – EMMA CRFs.The EMMA study mother’s visit data extraction form (see Additional file 4). This form contains the basic information to be extracted from the individual’s medical record for visits to the clinic. This process allows us to create a longitudinal dataset (multiple visits for each patient) to complete the data analysis to create the primary and secondary study outcomes for each study participant (the mother);The EMMA study mother-infant data extraction form (see Additional file 4). This form contains the basic information needed to assess primary and secondary outcomes for the infant (date of delivery, dates of HIV tests, etc.). Date of delivery from the mother-infant form is also then merged into the mother’s longitudinal database to create the key primary and secondary outcomes for the mother;The EMMA study Mentor Mother/patient visit record form (see Additional file 4). At the sites providing the EMMA intervention, Mentor Mothers will complete the Mentor Mother/patient visit record form after each exit visit with a mother. This form will just record the date of the visit, the mother’s name and clinic ID number, a field to indicate if an SMS message was scheduled to be sent to the mother at this visit, and a field to indicate if a reminder was set up on the mother’s phone. The Mentor Mother will complete this form for all patients at the site during the study intervention period. These forms then become part of the patient’s medical file. The study will extract data from this form for patients enrolled in the study.

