### Data entry and storage

Each subject will be assigned a four-digit study identification number to be used to store and analyze data. The first two digits will indicate the study site (01–12) and the next two digits will be assigned sequentially as patients enroll in the study (01–30). KEMRI/WRP data entry clerks will input the relevant information from medical records (as outlined above) to the patient visit database (the study database will be developed using ClinPlus by the Data Coordinating and Analysis Center of the US Military HIV Research Program (MHRP)).

Password-protected computers for data entry are in lockable offices at the KEMRI/WRP headquarters in Kericho and the rooms are locked when not in use. All forms used for extracting information from clinical files will be stored in locked cabinets within locked offices.

The study database will be managed and maintained on a MHRP secure server by the Data Computing and Analysis Center (DCAC) in Bethesda, MD. The study database will be password-protected, with access limited to the study team. The linking file, which will contain name, clinic ID, and study ID, will be stored separately. We will run data cleaning routines regularly and generate queries to return to the site for resolution as needed.

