### Study monitoring

All of the patient-level data used for this study will be extracted from information routinely collected at the study sites and contained in patient medical records (paper files for the mother’s visit extraction form and the mother-infant form; electronic file for the Mentor Mother/Patient Encounter).

As these forms are completed over time based on the study schedule, they will be checked for completeness by the study coordinator. If any changes to forms are made, the original data will be left and crossed out and the corrected data will be written next to it with a signature and date of the person who made the change. The Study Coordinator will provide monthly updates on study enrollment numbers to the PI for monitoring enrollment progress.

Given the largely observational nature of this study, monitoring will focus upon, but not be limited to, informed consent, patient confidentiality, regulatory components (e.g. IRB approvals), and IRB reports. The PI will conduct monitoring activities every six months, in which an experienced study coordinator and data manager working with Walter Reed/KEMRI program in Kericho will review 100% of informed consents and a 10% sample of all newly completed forms and entered data since the last monitoring visit and compare to original medical records. If any issues are found during regulatory monitoring activities, a one-time monitoring visit will be done within a period of three months and staff will be retrained. For this minimal risk study addressing behavioral and staff management issues, a data monitoring committee was not organized [26].

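### A dated visit record kept only in the EMMA arm is counted among the evaluation data and filed with the outcome source, so completeness of outcome ascertainment may differ by arm

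*Protocol article*

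**What the plan says.** Follow-up is passive, by record review. Data collection methods says that what the evaluation needs will come from routinely collected care information in both arms, "as well as the additional information routinely collected by the Mentor Mother providing EMMA as part of her interactions with patients". It admits that routine records at these and other sites have often been incomplete: "failure to enter visit dates, drugs prescribed, recording negative HIV test results rather than leaving information blank". Study staff will therefore review each site's record system before the study starts.

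The same section describes three extraction forms. The mother's visit form, filled from her medical record, gives the maternal outcomes. The mother-infant form gives the infant outcomes and the delivery date. Neither is described as limited to one arm. The third form is limited to one arm: "At the sites providing the EMMA intervention, Mentor Mothers will complete the Mentor Mother/patient visit record form after each exit visit with a mother". Its content is narrow: "This form will just record the date of the visit, the mother’s name and clinic ID number, a field to indicate if an SMS message" (that is, whether one had been arranged). The only other field covers a reminder set on the mother's phone. On where it is kept: "These forms then become part of the patient’s medical file". Study monitoring says something different, listing paper files for the first two forms and an "electronic file for the Mentor Mother/Patient Encounter".

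The description of the EMMA intervention adds that the texting application stores message delivery status and dates, which the study team can consult to document reminders. Data entry and storage says that cleaning routines will generate queries for sites to resolve.

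Under Outcomes measures, P1 and P2 count supply as uninterrupted when drugs dispensed cover at least 90% of days. P2 runs from delivery to 24 weeks.

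**The concern.** Days covered can be computed only from dispensing entries that are present and dated. In the EMMA arm, the medical file as Data collection methods describes it holds a second, independent list of visit dates. An extractor who meets an undated dispensing entry could date it from that list. A Mentor Mother date with no matching clinic entry could prompt a further search, or a query to the site. No such form exists in an SOC file.

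At stake is confusion between better recording and better retention. A woman whose refill was dispensed but not recorded looks the same as a woman who missed it. If such gaps are closed more often in one arm, the primary comparison moves towards EMMA with no change in care. Adjustment for age, gestation, parity or site characteristics would not be expected to correct this.

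**Working it through.** The article gives no figure for record completeness or refill length, so there is no stated result to reproduce on this point. Table 1 is not in dispute.

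**1. What the form can and cannot do**

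| Item needed for P1–P3 | On the Mentor Mother form? |
|---|---|
| Visit date | Yes |
| Drug and quantity dispensed | No |
| Infant HIV result | No |

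The form cannot create a refill or a test result. It can supply a visit date, or show that a visit took place whose clinic entry is missing. Visit dates are among the items the article lists as commonly absent.

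**2. How sensitive P2 is to one missing entry**

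Inputs from Outcomes measures: window 24 × 7 = 168 days; threshold 90%.

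- Days required: 0.90 × 168 = 151.2, so at least 152 whole days.
- Uncovered days tolerated: 168 − 152 = 16.
- Coverage after losing one supply of L days, for a woman otherwise fully covered and with no carry-over: (168 − L)/168.

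| L (days, assumed) | Coverage | P2 |
|---|---|---|
| 14 | 91.7% | success |
| 16 | 90.5% | success |
| 17 | 89.9% | failure |
| 28 | 83.3% | failure |
| 56 | 66.7% | failure |
| 84 | 50.0% | failure |

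Carry-over does not rescue the monthly case. With 30 pills collected every 28 days and surplus carried forward, one missed entry leaves between 140/168 = 83.3% and 150/168 = 89.3%, depending on which entry is lost. Both are failures.

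P1 behaves similarly. For an illustrative window of 28 weeks (196 days), losing 28 days gives 168/196 = 85.7%, a failure; shorter windows are more sensitive.

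**3. Illustration only: how completeness turns into a false difference**

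Assume six 28-day entries in the window, entries missed independently, no true effect, and a proportion p of women truly uninterrupted in both arms. If a fraction q of entries is missed in the SOC arm only, the false difference is p × [1 − (1 − q)^6].

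| q | (1 − q)^6 | p = 0.40 | p = 0.65 | p = 0.80 |
|---|---|---|---|---|
| 1% | 0.941 | 2.3 points | 3.8 | 4.7 |
| 2% | 0.886 | 4.6 | 7.4 | 9.1 |
| 5% | 0.735 | 10.6 | 17.2 | 21.2 |

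None of q, p or the refill interval is in the article. The table shows only that the outcome magnifies small differences in recording. It does not estimate what will happen here.

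**The case against.** The strongest reply is that the article already assigns the outcomes to two forms not limited to one arm, and that the Mentor Mother form lists only a visit date, identifiers and two reminder fields. This stands. A reader might infer that P1–P3 are drawn from an EMMA-only source; the documents do not support that. The general sentence on information for the evaluation can be read as covering process data, and the form's SMS and reminder fields fit that use.

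The article also describes no cross-check of Mentor Mother dates against clinic entries, and a visit date alone does not show that drugs were dispensed. This stands too: the bias is a possible route, not an established fact, and no point figure for it can be claimed. But nothing in the text closes the route. The pre-study review covers every site and should reduce gaps in both arms, but it comes before extraction. The 10% check against original records does not bar an arm-specific source either.

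A reader might also infer that removing the form would blind extraction, or that the site digits in the study number are the problem. Arm is fixed by site, so anyone reading a site's files knows it regardless. The outcomes follow set rules, and recoding the clinic would complicate returning queries.

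Finally, extraction order and query rules may be in the full protocol or the supplementary forms. Their absence from an article is not held against it. The point rests on what the article does state: the source is counted in, and it is filed with the outcome record. If the Study monitoring description is the right one, the exposure during extraction is weaker, which is why the two descriptions need reconciling.

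**Conclusion.** The point holds as a conditional risk. An EMMA-only dated visit record is counted among the evaluation data and, on one of two conflicting descriptions, lies in the file from which maternal outcomes are extracted. It could help complete or query dispensing records in one arm only. One unrecorded supply of 17 days or more is enough to turn a fully covered woman into a P2 failure; a single loss of 16 days or fewer is not. Any resulting bias would favour EMMA. Its size is unknown, because refill length, recording rates and extractors' practice are not given. This is a worthwhile, cheap improvement, not a demonstrated error in the primary outcomes.

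**What to change.** 1. State that P1–P3 and S1–S6 are derived only from record sources present in both arms.
2. Use the Mentor Mother form and the SMS log for measures of intervention delivery only. Hold them apart from the file used for outcome extraction, and extract them after that woman's outcome forms are closed.
3. Apply one query rule for missing entries, the same in both arms, that never uses the Mentor Mother form or SMS log as a trigger or source.
4. Make Data collection methods and Study monitoring agree on where the Mentor Mother form is held.

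The cost is a few sentences in the extraction and query procedures and separate storage for an existing form. The downside is that a few true visits or dates known only from the Mentor Mother form go uncounted in the EMMA arm, as comparable unrecorded visits already do in the SOC arm.

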### Data entry and storage

Each subject will be assigned a four-digit study identification number to be used to store and analyze data. The first two digits will indicate the study site (01–12) and the next two digits will be assigned sequentially as patients enroll in the study (01–30). KEMRI/WRP data entry clerks will input the relevant information from medical records (as outlined above) to the patient visit database (the study database will be developed using ClinPlus by the Data Coordinating and Analysis Center of the US Military HIV Research Program (MHRP)).

Password-protected computers for data entry are in lockable offices at the KEMRI/WRP headquarters in Kericho and the rooms are locked when not in use. All forms used for extracting information from clinical files will be stored in locked cabinets within locked offices.

The study database will be managed and maintained on a MHRP secure server by the Data Computing and Analysis Center (DCAC) in Bethesda, MD. The study database will be password-protected, with access limited to the study team. The linking file, which will contain name, clinic ID, and study ID, will be stored separately. We will run data cleaning routines regularly and generate queries to return to the site for resolution as needed.

